## Statistical analysis plan

Categorical demographic and other baseline characteristics variables will be summarized by frequencies and percentages. Continuous variables will be summarized by both mean and standard deviation for data with normal distributions or median and inter-quartile range for non-normally distributed data. Either a Chi-square or Fisher’s exact test will be used to compare categorical variables between groups, while Mann–Whitney U-test or Student’s t-test will be used for continuous variables, if necessary.

The primary objective of this cohort is to evaluate the effectiveness of the self-management program, we plan to perform three separate analyses for the primary outcome. First, the incidence rate of composite endpoint events will be analyzed by the Chi-squared test. Second, time to occurrence of composite clinical endpoints will be analyzed using log rank test. The hazard ratio (HR) with 95% CI will be estimated by using the Cox proportional hazards model or competitive risk model. Third, growth mixture models and group-based trajectory models (GBTM) will be used to analyze the trajectories of exposure and outcome variables [48]. Covariates for the models will be selected based on prior knowledge and published papers. Logistic regression or Poisson regression will be used to analyze categorical outcomes. Liner mixed-effect model will be applied to the longitudinal data, such as the absolute change, and slope of eGFR and other secondary outcomes.

Even with some retention strategies, considerable missing data is expected over 5-years follow-up. The proportion of missing data will be summarized in each group and at each visit point. If there is less than 20% of data missing for the covariate data, we will perform a complete case analysis. If there is more than 20% of missing data, we will perform Little’s test and use multiple imputations under the assumption of missing is at random. Subgroup analyses will be conducted across baseline eGFR levels, demographic status and other factors, if possible. To test the credibility and robustness of the findings, several sensitivity analyses will be performed, including E-value and other advanced models [49]. Effect modification will be investigated using stratified analyses and formal tests of interaction. Mediation will be analyzed by adding the hypothesized mediators, one by one, to the confounder-adjusted models to study the extent to which they explain any association found.

All analysis will be performed in PASW 18.0 (SPSS Inc. IBM Corporation, Armonk, New York, USA) and STATA SE/15.0 (Stata Corp. College Station, Texas, USA).

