**Methods:**

In this ambispective intervention cohort study,1,200 patients with CKD stages 1–5 will be recruited from July 2015 to July 2024 in 3 branches of Guangdong Provincial Hospital of Chinese Medicine (GPHCM) in Guangdong province, China. The patients in the self-management cohort will choose to receive an intervention that consists of education, nutrition/diet modification, lifestyle change recommendation, medication review, and psychology support based on Social Cognition Theory (SCT). The patients in the control cohort will do regular follow-ups based on the clinic rules. All the patients will be followed up for 5 years, or until the occurrence of a primary outcome. Detailed clinical, laboratory markers, nutritional status, psychological exposures and outcome questionaries will be collected semiannually in CKD stage 1–2 and trimonthly in stage 3–5 patients. The primary outcome is the occurrence of composite clinical endpoints (doubling of serum creatinine level, ESKD, loss of renal function (≥ 40% decline in GFR from baseline), death, major cardiovascular or cerebrovascular events). The main secondary outcomes include the absolute change and slope of eGFR, absolute changes of urinary protein creatinine ratio, 24-h urine proteinuria, intact parathyroid hormone level, and self-management adherence rate and quality of life from baseline to end of the study. The effectiveness of self-management will be analyzed and the association between longitudinal trajectories of self-management and renal outcomes will be evaluated.

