## Methods

### Study design and study population

An ambispective cohort study will be conducted in the department of nephrology at the three branches of Guangdong Provincial Hospital of Chinese Medicine (GPHCM) in Guangdong province, China. Two branches are located in different Districts in Guangzhou city (Yuexiu and Fangcun District) and one in Zhuhai city. The study population includes all CKD 1–5 patients (speak Cantonese or Mandarin) attending the CKD consultation outpatient clinic in GPHCM from July 2015 to July 2024. Of 200 CKD patients were already registered in the retrospective cohort from July 2015 to July 2019 and they will keep following in the prospective cohort. Beginning in August 2019, a prospective cohort will be built on. All the patients will be followed for at least 5 years, or until the occurrence of a primary outcome.

CKD is defined by a glomerular filtration rate (GFR) < 60 mL/min/1.73 m2 or markers of kidney damage, or both, of at least 3 months duration [5]. GFR is calculated by CKD-EPI equation, and CKD staging will use the Kidney Disease Outcomes Quality Initiative (KDOQI) definition [29]. Patients are eligible for inclusion if they are Chinese, aged 18 to 80 years, have CKD (Stages 1–5), and give a written signed informed consent. Exclusion criteria for the study are psychosis or unable to cooperate with clinical staff for other reasons and have a history of dialysis or renal transplant.

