## Sample size calculation

We selected the occurrence of composite endpoints as the primary study outcomes to calculate the sample size. Previous studies have reported that the composite endpoints rate range from 18.1–126/1,000 person-years [46, 47]. Based on these studies and our previous data, we estimated that the incidence rate of a composite endpoint in our cohort would be 60/1,000 person-years. There are about 30 variables that may affect prognosis, and there should be at least 10 endpoints per variable. Thus, we anticipate that recruiting 1,200 participants with 300 events over a 5-year follow-up will ensure adequate statistical power.

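### The first of three unranked primary analyses applies a chi-squared test, which ignores time at risk, to an incidence rate, so unequal withdrawal alone can inflate its false-positive rate

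*Protocol article*

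**What the plan says.** All references are to the protocol article.

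- **Statistical analysis plan.** For the effectiveness objective, "we plan to perform three separate analyses for the primary outcome". No order of importance is given. The first is "First, the incidence rate of composite endpoint events will be analyzed by the Chi-squared test". The next is "Second, time to occurrence of composite clinical endpoints will be analyzed using log rank test", with a hazard ratio from a Cox or competing-risk model. The third is trajectory modelling. Poisson regression is named in the same section, for categorical outcomes.
- **Sample size calculation.** The planning assumption is that "the incidence rate of a composite endpoint in our cohort would be 60/1,000 person-years". Here the article uses incidence rate with a person-time denominator.
- **Loss to follow-up.** The Statistical analysis plan section says that "considerable missing data is expected over 5-years follow-up", and the Discussion treats high loss as unavoidable. No percentage is given.
- **Cohorts.** Under Screening and Enrollment, patients who decline the programme form the control cohort and are followed by the clinic's own rules. Allocation is by choice, and no ratio is stated.
- **Window.** Outcome measures counts primary-outcome events during the five-year follow-up.

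**The concern.** The measure and the test do not match. A rate divides events by time at risk. A chi-squared test on a two-by-two table divides events by patients. A patient lost at year 1 without an event must then either count the same as one observed event-free for five years, or be removed while patients with early events stay in. Neither is harmless when loss differs between the cohorts: the first lowers the observed proportion where loss is higher, and the second raises it.

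Equal retention cannot be taken for granted when patients choose their own cohort and one cohort has far more contact with the study team. The issue is separate from confounding, because it arises even when both cohorts have the same true event rate. At stake is a listed primary analysis that could show a difference produced by withdrawal and could disagree with the log-rank result on the same data.

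**Working it through.** **The plan's own figures.** "There are about 30 variables that may affect prognosis, and there should be at least 10 endpoints per variable": 30 × 10 = 300 events, as stated. At 0.06 per year over 5 years, with follow-up ending at the first event and no loss, the risk is 1 − exp(−0.3) = 25.9%, or 1,200 × 0.259 = 311 events. The rate and the event target are therefore broadly consistent.

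**Inputs.** From the article: event rate r = 0.06 per year, T = 5 years, 1,200 patients. Assumed, because the article gives no figure: 600 per cohort, two-sided 5% level, the same true rate in both cohorts, exponential withdrawal unrelated to the outcome, and five-year loss L (the probability of withdrawing within 5 years if no event occurs) between 10% and 40%.

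**Formulas.** Withdrawal hazard m = −ln(1 − L)/5.

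- Withdrawn patients counted as event-free: p = r/(r + m) × [1 − exp(−5(r + m))].
- Withdrawn patients dropped: p′ = p/(p + s), where s = exp(−0.3) × (1 − L) is the probability of completing 5 years event-free.

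**Worked case, 20% v 40% loss.**

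- L = 0.20: m = 0.0446; p = 0.06/0.1046 × (1 − 0.5927) = 0.234; p′ = 0.2336/(0.2336 + 0.5927) = 0.283.
- L = 0.40: m = 0.1022; p = 0.06/0.1622 × (1 − 0.4445) = 0.206; p′ = 0.2055/(0.2055 + 0.4445) = 0.316.

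The cohort with more loss looks better under the first rule (20.6% v 23.4%) and worse under the second (31.6% v 28.3%), although the true rates are identical. For the first rule, the difference is 0.028 and its standard error is √(0.2196 × 0.7804 × 2/600) = 0.0239, so z = 1.17. The test then rejects with probability of about 22%.

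**False-positive rates by simulation** (3,000 runs per row; simulation standard error about 0.4 percentage points near 5%):

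| Five-year loss | Observed proportions, counted event-free | Observed proportions, dropped | Chi-squared, event-free | Chi-squared, dropped | Log-rank | Person-time rate ratio |
|---|---|---|---|---|---|---|
| 20% v 20% | 23.4% v 23.4% | 28.3% v 28.3% | 4.8% | 4.6% | 4.3% | 4.4% |
| 10% v 20% | 24.7% v 23.4% | 27.0% v 28.3% | 8.0% | 6.3% | 4.5% | 4.5% |
| 10% v 30% | 24.7% v 22.0% | 27.0% v 29.8% | 18.7% | 15.6% | 4.6% | 4.7% |
| 20% v 40% | 23.4% v 20.6% | 28.3% v 31.6% | 22.1% | 19.4% | 4.8% | 5.0% |
| 10% v 40% | 24.7% v 20.6% | 27.0% v 31.6% | 39.3% | 33.9% | 5.7% | 5.6% |

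On the same simulated data, the two methods that use follow-up time stay near 5% throughout.

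**The case against.** The strongest reply is that the plan already contains the right analysis. The log-rank test and the hazard ratio follow directly after the chi-squared test, with covariates chosen from prior knowledge and an E-value sensitivity analysis. An unadjusted chi-squared test could not carry an effectiveness claim in a non-randomised cohort anyway. This stands, and it limits the point to one analysis of three. It does not remove the point, because the article gives that analysis the same standing as the others.

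Four stronger readings are tempting, and the documents do not support them.

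- **That withdrawal will differ.** Both cohorts are registered in the same clinic, the hospital is their designated insurance provider, and events are also taken from the hospital record, so a missed programme visit need not mean unknown event status. The article does not make clear whether the retention measures cover controls. Unequal loss is possible, but it is not shown to be likely.
- **That the test shows a difference whenever loss differs.** The expected proportions differ, but the test still fails to reject in most simulated studies, including about 78% of them at 20% v 40% with withdrawals counted as event-free.
- **That the observation window is open-ended.** The abstract says "All the patients will be followed up for 5 years, or until the occurrence of a primary outcome", and Study design and study population says "All the patients will be followed for at least 5 years, or until the occurrence of a primary outcome". A reader might infer that early recruits have longer to accrue events. Outcome measures, however, ties the primary outcome to five years, and longer follow-up would bias the comparison only if recruitment dates differed between cohorts, which is not shown.
- **That a handling rule for withdrawn patients is missing.** An article may leave this to the analysis plan. The multiple-imputation sentence might also be read to cover outcomes, although the 20% threshold before it is worded for covariates. The finding is the stated test, not the absent rule.

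Incidence rate may also be loose wording for cumulative incidence. If so, the measure is a proportion, but the test still needs known five-year status for every patient, and that is what loss removes.

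**Conclusion.** The point holds for the first listed primary analysis only. A chi-squared test on patient counts does not suit an incidence rate in a cohort where considerable loss is expected. The size depends on how unequal the loss is: no inflation with equal loss, slight at 10% v 20%, and roughly four times the nominal 5% at 20% v 40%. These figures rest on assumed withdrawal percentages, a 1:1 split, a two-sided 5% level and withdrawal unrelated to the event. The mechanism is certain, but its size in this study is not known. The log-rank and Cox analyses are not affected by it. The point merits correction but does not undermine the primary evaluation as a whole.

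**What to change.** Replace the chi-squared test with one of these:

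1. Events per person-year in each cohort, with a Poisson rate ratio and a person-time offset.
2. The Kaplan-Meier five-year risk difference with its confidence interval.

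In either case, censor withdrawn patients at the last date of known event status, and count events within five years of baseline, as Outcome measures already implies. Alternatively, name the time-to-event analysis as the primary one and label the chi-squared test descriptive.

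The cost is a change of wording. Poisson and survival methods are already in the plan, and no new data are needed. The change does not protect against withdrawal that is related to prognosis. That assumption should be stated with the result.

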### Screening and Enrollment

Research assistants in our team are responsible for identifying patients from retrospective cohort and consultation outpatient in the Department of Chronic Disease Management at GPHCM to ensure they meet inclusion criteria. Considering the retrospective cohort is an observational cohort, this study will use the date when the patients are enrolled in the new cohort as their baseline time. After pre-evaluation, nurses will first make an appointment and then explain the study to candidates through a face-to-face interview and answer any questions they have. If the patients do not agree to enroll in SMP-CKD cohort, they will be registered in the chronic disease management clinic in GPHCM and do regular follow-up based on the clinic rules (as the control cohort). After confirming eligibility, all participants will sign an informed consent. (Study process can be found in Fig. 1).

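### Crude chi-squared and log-rank tests share primary status with a Cox model that has planned covariates, the cohorts are self-selected, and no analysis is named as decisive

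*Protocol article*

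**What the plan says.** The cohorts are formed by patient choice. The abstract (Methods) states: "The patients in the self-management cohort will choose to receive an intervention that consists of education". Under Screening and Enrollment the other side is equally plain: "If the patients do not agree to enroll in SMP-CKD cohort, they will be registered in the chronic disease management clinic in GPHCM", and these patients serve as the control cohort.

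The Statistical analysis plan gives effectiveness as the primary objective and says "we plan to perform three separate analyses for the primary outcome":

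- **First:** "First, the incidence rate of composite endpoint events will be analyzed by the Chi-squared test".
- **Second:** "Second, time to occurrence of composite clinical endpoints will be analyzed using log rank test". The same item adds a hazard ratio with 95% CI, "estimated by using the Cox proportional hazards model or competitive risk model".
- **Third:** growth mixture and group-based trajectory models for exposure and outcome variables.

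The section then says that covariates for the models will be chosen from prior knowledge and the literature. It later refers to confounder-adjusted models and plans an E-value as a sensitivity analysis. No strata, weights or covariates are attached to the chi-squared or log-rank test, and no analysis is named as the one that decides effectiveness.

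The Outcome measures section makes death from any cause a component of the composite.

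**The concern.** Patients who accept a demanding self-management programme probably differ from those who refuse it in motivation, disease stage and comorbidity. Any of these may also predict the composite. A test that uses no covariates attributes such differences to the programme. The Sample size calculation counts about 30 variables that may affect prognosis, and neither test uses any of them.

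With no ranking, a significant chi-squared or log-rank result could be reported as a primary result even if the covariate-adjusted hazard ratio showed nothing.

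Two wording faults add to this:

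- A chi-squared test compares proportions with an event. It does not compare incidence rates, because it takes no account of time at risk. The protocol itself expects considerable missing data and, in the Discussion, treats high loss to follow-up as inevitable.
- The competing-risk option has no evident competing event when the outcome is the full composite, because death already counts as an event.

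**Working it through.** **Inputs from the protocol (Sample size calculation).** About 30 variables × 10 events each = 300 events, which reproduces the stated figure. Also stated are 1,200 participants, 5 years and 60 events per 1,000 person-years. At that rate, 1,200 × (1 − e^(−0.06×5)) = 311 events, or 1,200 × 5 × 0.06 = 360 on a simple linear count. The point here does not depend on that difference. The illustration uses 300/1,200 = 25% five-year risk.

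**Assumptions, not in the protocol.** Equal cohorts of 600, true HR 1, two-sided 5% tests, and one binary adverse factor with hazard ratio c. Its prevalence is p1 in the programme cohort and p0 in the control cohort. The protocol gives no strength, prevalence, imbalance or allocation ratio, so a range is shown.

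**Approximation.** Apparent HR ≈ [p1·c + (1 − p1)] / [p0·c + (1 − p0)], and z = ln(HR) × √(300 × 0.25) = ln(HR) × 8.66.

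- c = 2, 45% vs 55%: 1.45/1.55 = 0.935; |z| = 0.58; about 9% significant.
- c = 2, 40% vs 60%: 1.40/1.60 = 0.875; |z| = 1.16; about 21%.
- c = 3, 40% vs 60%: 1.80/2.20 = 0.818; |z| = 1.74; about 41%.
- A stronger case, with a favourable factor of HR 0.4 in 70% of choosers and 30% of decliners: 0.58/0.82 = 0.707; |z| = 3.00; about 85%.

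**Simulation (2,000 runs per row, all followed for 5 years unless an event occurs).**

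| Factor HR | Prevalence, programme vs control | Crude HR | Chi-squared | Log-rank | Log-rank stratified on factor |
|---|---|---|---|---|---|
| 2 | 50% vs 50% | 1.00 | 5.3% | 5.0% | 4.95% |
| 2 | 45% vs 55% | 0.935 | 9.35% | 9.25% | 5.3% |
| 2 | 40% vs 60% | 0.874 | 20.2% | 20.6% | 4.55% |
| 3 | 45% vs 55% | 0.902 | 13.6% | 12.85% | 5.7% |
| 3 | 40% vs 60% | 0.813 | 40.6% | 40.5% | 4.7% |

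The simulation agrees with the approximation. The two crude tests reject at nearly the same rate when follow-up is equal. Stratifying on the factor returns the error to nominal within simulation noise (standard error √(0.05 × 0.95/2,000) ≈ 0.5 percentage points).

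**Chi-squared test with unequal follow-up.** Assume equal hazards of 0.06 per year, no confounding, 600 per cohort, and potential follow-up of 4.5 years in one cohort and 3.5 in the other. The proportions are 1 − e^(−0.27) = 23.7% and 1 − e^(−0.21) = 18.9%. The pooled proportion is 0.213 and the standard error √(0.213 × 0.787 × 2/600) = 0.0236, so z ≈ 2.0 and about half of such tests are significant. The cohort followed longer looks worse. These times must be potential follow-up: because follow-up stops at an event, mean observed time over 5 years at this hazard cannot exceed (1 − e^(−0.3))/0.06 = 4.32 years.

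**Competing risks.** In an analysis of time to first composite event, death from any cause is an event. It cannot also be a competing event. It does compete when a component without death, such as ESKD, is analysed alone.

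**The case against.** A reader might infer that the first two primary analyses are wholly unadjusted, or that the plan contains no adjusted effect estimate. The protocol does not support either reading. The second analysis includes a model-based hazard ratio, which is the only effect estimate with an interval named for the primary outcome. Covariates for the models are provided for, confounder-adjusted models are mentioned, and an E-value is planned. Sizing the study on about 30 prognostic variables makes sense only for a multivariable model. The Discussion acknowledges selection bias and confounding, although it attributes them to the hospital-based design and not to self-selection.

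Nor does the protocol say that a crude p-value will be the headline result. Presenting crude comparisons before adjusted ones is ordinary in cohort studies. The third analysis is not described as a between-cohort test, so it is hardly a third chance of a positive result. The two crude tests behave almost alike under equal follow-up, so little is gained by choosing between them. The confounder sizes are assumed. The follow-up example could also work against the programme, if its patients are the better retained.

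All of this stands, and it lowers the severity. It does not answer the remaining point: the crude tests are listed as primary-outcome analyses on equal terms with the Cox model. A sensitivity analysis such as the E-value does not correct a crude p-value. This is not detail left to a fuller plan, because the article itself fixes these tests.

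**Conclusion.** The concern holds as one of ranking and wording. Two tests that cannot separate a programme effect from self-selection have the same standing as a hazard ratio for which adjustment is planned, and nothing says which decides. Under no true effect, with equal cohorts and 300 events, the crude tests give about 9% to 41% false positives for the moderate imbalances tried, and more (about 85%) under a strong one. These figures illustrate a range and do not predict this cohort. They also take the imbalance to favour the programme; if sicker patients opt in, the bias would run the other way and could hide a benefit.

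The chi-squared test does not test the rate it is said to test, and it is invalid if potential follow-up differs between cohorts, with bias in either direction. The competing-risk option does not fit the full composite. This should be fixed before analysis. It is not a must-fix defect, because adjusted estimation is already in the plan.

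**What to change.** - Name one primary analysis: a confounder-adjusted Cox model for time to first composite event, using baseline variables the protocol already plans to collect. Its hazard ratio and 95% CI decide effectiveness.
- Label the chi-squared and log-rank results descriptive. Alternatively, replace them with event rates per person-time and adjusted or weighted survival curves.
- Drop the competing-risk alternative for the full composite, and restrict it to analyses of components that exclude death.
- Keep the E-value for confounding that remains unmeasured, since adjustment removes only what is recorded.

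The cost is a few sentences of plan wording, slightly more analysis work and a somewhat wider adjusted interval. No new data are needed.

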### Follow-up and Retention

After the pre-evaluation of the baseline variables, a corresponding individualized follow-up calendar will be formulated. If there are no special circumstances, visits will be conducted semiannually in stage 1–2 patients and trimonthly in stage 3–5 CKD patients. Flexibility of 1 week before or after the next visit is allowed. The timeline can be found in Table 1.

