### Outcome measures

The primary outcome is the occurrence of composite clinical endpoints (doubling of serum creatinine level, ESKD(eGFR < 15 ml/min for CKD 1–4 patients; or dialysis for at least 30 days or kidney transplant for patients with CKD 1–5), loss of renal function(≥ 40% decline in GFR from baseline), death(from any cause), major cardiovascular or cerebrovascular events) during the 5-year follow up (shown in Table 4) [44, 45]. Those outcome data will be collected through the outcome assessment scale during each visit by reviewing the laboratory test results and the medical record in Hospital Information System (HIS).

**Table 4 Tab4:** Definition of composite clinical endpoints

Clinical events	Definition
1.A doubling of serum creatinine levels	Doubling of the serum creatinine level from baseline sustained for at least 30 days according to central laboratory assessment
2.End-stage kidney disease (ESKD)	eGFR < 15 ml/min for CKD 1–4 patients; or dialysis or kidney transplant for CKD 1–5 patients
3.Loss of renal function	≥ 40% decline in GFR from baseline
4.Death	Death from any cause
5.Major cardiovascular or cerebrovascular events	Acute heart failure, myocardial infarction, ischemic cerebral infarction or intracranial hemorrhage

The main secondary outcomes include the absolute change and slope of eGFR, absolute changes of urinary protein creatinine ratio, 24-h urine proteinuria, intact parathyroid hormone level (iPTH), and self-management adherence rates (evaluated by self-management behavior questionnaire) and quality of life. Other outcomes include serum creatinine level (SCr), blood urea nitrogen level (BUN), plasma albumin, triglyceride, cholesterol, calcium, phosphate and other Laboratory markers and cardiovascular function.

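### The log-rank test of the primary composite pools CKD stages 1–5 in self-selected cohorts, so any stage imbalance confounds it; it should be stratified by baseline stage

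*Protocol article*

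**What the plan says.** The Statistical analysis plan section of the Protocol article lists three analyses of the primary outcome. The second reads: "time to occurrence of composite clinical endpoints will be analyzed using log rank test". The next sentence adds: "The hazard ratio (HR) with 95% CI will be estimated by using the Cox proportional hazards model or competitive risk model".

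Three other statements in that section bear on baseline stage:
- Covariates: "Covariates for the models will be selected based on prior knowledge and published papers". None is named.
- Subgroups: "Subgroup analyses will be conducted across baseline eGFR levels, demographic status and other factors, if possible".
- Stratified analyses are planned, but to examine effect modification and not for the primary comparison.

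Outcome measures, Table 4, defines the ESKD component as "eGFR < 15 ml/min for CKD 1–4 patients; or dialysis or kidney transplant for CKD 1–5 patients". The loss-of-function component, "≥ 40% decline in GFR from baseline", applies to every stage.

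Under Screening and Enrollment, patients who do not agree to join the programme cohort are followed in the clinic as the control cohort.

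**The concern.** Two features of the design meet in the log-rank test.

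First, baseline stage drives the event rate. Some of this is biology and some is the definition: a stage 4 patient just above eGFR 15 needs a very small fall to have an event, while a stage 5 patient just below 15 cannot use that limb at all.

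Second, patients choose their own cohort. If willingness to join varies with disease severity, the cohorts will differ in stage mix.

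An unstratified log-rank test then compares the stage mix as well as the programme. It has no place for covariates, so the sentence on covariate selection protects the regression model but not this test. A p-value from one of the three named primary analyses could therefore reflect who enrolled and not what the programme did. If stage happens to be balanced, the cost is smaller: some lost power and a hazard ratio pulled towards 1.

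**Working it through.** **The plan's own figures (Sample size calculation).** 30 variables × 10 events = 300 events, as stated. 1,200 patients at 60 per 1,000 person-years over 5 years give 1,200 × (1 − e^(−0.06×5)) = 311 events, which covers 300. At 300 events and a 1:1 split, power is about 70% for HR 0.75, and the HR detectable with 80% power is 0.72. There is little power to spare.

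**How the endpoint depends on stage (Table 4).** The relative eGFR fall that triggers an eGFR-based event is min(40%, 1 − 15/eGFR₀) for baseline eGFR₀ ≥ 15, and 40% below 15.

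| Baseline eGFR | Fall needed |
|---|---|
| 60 | 40% |
| 25 | 40% |
| 20 | 25% |
| 18 | 17% |
| 16 | 6% |
| 14 (stage 5) | 40% |

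The hurdle drops through stage 4 and jumps back at 15, so stage-specific hazards can differ strongly and not in order of eGFR.

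**Setting for the calculations.** The plan gives no stage-specific rates. As an assumption, two risk groups take the ends of its cited range, 18.1 and 126 per 1,000 person-years, mixed 61.2% : 38.8%: 0.612 × 18.1 + 0.388 × 126 = 60.0, the plan's average. Also assumed: 1,200 patients, 1:1, exponential times, 5 years, no loss, two-sided 5% test.

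**Imbalance, no programme effect.** Let the high-risk share be 33% in the programme cohort and 45% in the control cohort.
- Programme: 0.33 × 126 + 0.67 × 18.1 = 53.7 per 1,000 person-years.
- Control: 0.45 × 126 + 0.55 × 18.1 = 66.7.
- Crude ratio at the start: 53.7 / 66.7 = 0.81, with no effect present.

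In repeated simulations the pooled test rejected 45–48% of the time with HR 0.79–0.81. The stratified test rejected about 5% with HR 1.00–1.01. With a small imbalance (36% v 41%) the pooled test rejected 11–13% and the stratified test about 6%.

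A five-stage version assumed hazards of 18.1, 30, 60, 126 and 100 and 1,500 replicates:

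| Stages 4–5, programme v control | Pooled HR | Pooled rejection | Stratified HR | Stratified rejection |
|---|---|---|---|---|
| 24% v 36% | 0.81 | 47% | 1.00 | 4.5% |
| 48% v 22% | 1.48 | 95% | 0.99 | 5% |

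The bias can go either way.

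**Stage balanced, programme effective.** Two-group setting, 3,000 replicates per HR:

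| True HR | Pooled power | Stratified power |
|---|---|---|
| 0.65 | 86% | 91% |
| 0.70 | 73% | 81% |
| 0.75 | 55% | 63% |
| 0.80 | 36% | 43% |

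The five-stage version gives a smaller loss: at HR 0.72, 74.5% pooled against 78.5% stratified, with the HR moving from 0.73 to 0.72.

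**Stage as an ordinary covariate.** In the two-group setting at HR 0.70 (400 replicates), a Cox model had 69% power unadjusted, 78.5% with the risk group as a covariate and 78.5% stratified. In the five-stage setting with 24% v 36%, stage as a categorical covariate gave HR 0.99 when the truth was 1.0 and 0.73 when it was 0.72.

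**Visit interval alone.** With equal hazards in every stage, gross stage imbalance and 6- against 3-month visits, the pooled HR was 0.99 and rejection 4.3%.

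**The case against.** The strongest reply is that the effect estimate comes from a regression model with covariates, that the section refers to confounder-adjusted models, and that the sample size allows for about 30 prognostic variables. A journal article may leave the covariate list to a fuller plan. All of that stands for the model. It does not reach the log-rank test, which the article names as a primary analysis and which cannot take covariates.

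Three stronger readings are tempting, and the documents do not support them.

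- **That the Cox model pools all stages unadjusted.** The article does not say so. Baseline stage is neither included nor excluded.
- **That only a separate baseline hazard for each stage can repair the problem.** Stage as a categorical covariate recovered the full gain above. Those simulations had proportional stage hazards; if the hazards are not proportional, a stratum protects further. A jump at eGFR 15 could also leave residual bias after linear or log eGFR adjustment, but the illustration of this needed assumed opposite uptake in stages 4 and 5 and had only 60 replicates. It carries no weight here.
- **That the stage-dependent visits distort the hazard ratio.** The schedule reads "visits will be conducted semiannually in stage 1–2 patients and trimonthly in stage 3–5 CKD patients" and "Those outcome data will be collected through the outcome assessment scale during each visit", so detection does differ by stage. Taken alone, its effect on the HR was negligible.

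Nor is restricting the eGFR limb to stages 1–4 an error in itself: a stage 5 patient would meet it at entry.

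**Conclusion.** The point holds for the log-rank test. As written it pools stages 1–5, in cohorts formed by patient choice, for an endpoint whose definition depends on stage. The serious consequence is confounding. A 12-point difference in the high-risk share is enough to push the false rejection rate to about 45% and the HR to about 0.8. The power loss under balance is secondary, about 4–8 points for stage hazards within the plan's 18.1–126 per 1,000 person-years.

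The stage mix, stage hazards, size and direction of imbalance, 1:1 split, target HR and absence of loss are all assumptions. The documents give none of them, so the sizes are illustrative. That an unstratified test is exposed to stage imbalance does not depend on them. The change should be made; it costs very little.

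**What to change.** In the Statistical analysis plan section, state that:
- the log-rank test for the composite is stratified by baseline CKD stage (1–2, 3, 4, 5);
- the Cox or competing-risk model includes baseline stage as a stratum or categorical factor, with baseline eGFR as a continuous covariate;
- the HR from that adjusted model is the main estimate of the programme effect.

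The last item matters because the stratified log-rank test deals with stage but not with other differences between self-selected cohorts.

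The cost is a sentence or two. Stage is already known for every patient because it sets the visit calendar. The HR becomes a within-stage HR and, if stage is a stratum, no HR for stage itself is estimated. Four strata with about 300 events should cost negligible efficiency. No visit schedule, endpoint definition or clinical rule changes.
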